### Implementation strategies

*HELM*. Principals, their distributed leadership teams (DLT), and school district-level leaders (e.g., Elementary Education Director, Director of Student Learning, etc.) will participate in HELM. HELM is a 9-month, data-driven organizational and leadership implementation strategy that entails eight core components: 1) Assessment and Feedback. 360º surveys measuring implementation leadership and climate are administered to principals and educators at three time points. These data will be synthesized into a detailed feedback report, which will be shared with the DLT and used to create a tailored leadership development plan to support implementation coaching throughout the year. 2) Initial Training. A 4-h didactic and interactive training will be provided to principals, their DLT, and district-level leaders and cover developing strategic implementation leadership behavior and building a positive EBP implementation climate in their schools. 3) Leadership Development Plan. During the initial training, principals and their DLT work individually with their HELM coach to review their 360º assessment data and develop goals for improving implementation leadership and climate. 4) Individual Coaching. HELM coaches provide monthly 1-h coaching sessions in person or via Zoom to review progress and update the leadership development plan. The coaching structure includes reflective questions about 1) broader school updates (10 min); 2) EBP implementation (10 min); 3) Leadership Development Plan progress (20 min); 4) barriers to implementation and solution generation (10 min); 5) next steps (5 min); and 6) “what other support is needed” from the district and/or HELM coaches (5 min). 5) Group *Coaching*. Coaches offer *optional* monthly 1-h group coaching calls with all HELM principals and DLT in each Cohort to review progress and share strategies across schools for idea generation and implementation support (this component is optional because there were mixed results in our pilot where some schools found Group Coaching helpful and others felt it was burdensome). 6) Organizational Strategy Development. Two 1-h meetings with district-level leaders are held, one in Fall semester and one in Spring semester of study enrollment to develop and update an organizational Climate Development Plan. This meeting will provide a structured discussion of alignment between school-level and district efforts to support EBP implementation. 7) Professional Learning Collaboratives. Two professional learning collaboratives are held with principals and their DLT to review content (align HELM strategies with principles from the National Educational Leadership Standards and EBP sustainment for the following school year) and share strategies across participants. 8) Graduation. During graduation, principals’ and their DLT team’s final feedback is reviewed, and progress for the past year is celebrated. Results from the pilot suggest HELM is feasible to deliver, meets the needs of school leaders, and allows school leaders to support EBP use.

*PBIS training*. Standard PBIS implementation includes initial training and technical assistance (i.e., booster training, fidelity monitoring, and coaching) – cornerstone implementation strategies across programs and domains [47] – which all participating schools will receive regardless of condition. Implementation Coaches will help schools form internal school implementation teams comprised of five to six members (e.g., teachers, administrators, community mental health providers, families). Implementation Coaches will provide ongoing support for the schools throughout the school year, inclusive of four booster training events (approximately 4–6 h) that will use progress monitoring data to determine specific skill building during the school year for all PBIS school implementation teams.

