**Methods:**

This study will use a hybrid type 3 effectiveness-implementation trial to provide a rigorous test of the effects of HELM in elementary schools. Schools will be randomly assigned to HELM + PBIS training and technical assistance (*n* = 21 schools; n = 210 educators) or PBIS training and technical assistance only (*n* = 21 schools; n = 210 educators) in a 1:1 ratio within cohorts using covariate constrained randomization that accounts for degree of prior PBIS exposure (measured using the Tiered Fidelity Inventory at baseline) and school size. A series of mixed effects models (time within educator, educator within school) will test within-subject/between-subject interactions across three timepoints (12 months total) to examine whether HELM will show steeper gains than the control on implementation leadership (primary outcome), implementation climate, PBIS fidelity, and student outcomes. Mediational analyses will test hypothesized mechanisms of change (i.e., implementation leadership and climate) of HELM on PBIS fidelity. Sequential mixed-methods data collection and analyses will further explore how organizational mechanisms are linked to implementation outcomes. Cost-effectiveness analyses will compare costs and outcomes of PBIS training and technical assistance only versus PBIS implementation with HELM.

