### Participants

Participating schools (*N* = 42) will be recruited into three cohorts (*n* = 14 schools p/cohort) from districts located in Washington state using a stratified recruitment approach. Schools will be compensated $400 total to support time for recruitment, retention, and other research activities. Inclusion criteria for districts are: 1) presence of a district-wide commitment to implement PBIS in elementary schools, as evidenced by either having completed a PBIS training in the past two years from certified coaches or a willingness to complete the training at the outset of study participation; 2) data sharing agreements with the project investigative team (including sharing of administrative data regarding students); 3) commitment to help recruit 10 educators per elementary school to complete study assessments (*N* = 420); and 4) no previous HELM exposure. Principals and leadership teams will participate in HELM for schools assigned to that condition. The research team will invite all educators from the school to participate in surveys and PBIS trainings and contacted by email or phone to complete informed consent. We will gather de-identified school administrative data for students in each classroom with no identifiable information and, therefore, active parental permission is not needed.

*Randomization*. Random assignment will occur at the school building level because both HELM and PBIS are building-level processes. The study methodologist will generate the randomization sequence, with allocation concealed from all other study personnel and participants. We will randomize schools within cohorts with equal probability (1:1) to: 1) PBIS + HELM; or 2) standard PBIS training and technical assistance. We will use covariate constrained randomization that accounts for degree of prior PBIS implementation and school size [45, 46]. Covariate constrained randomization enumerates a large number of possible assignments of the interventions to schools and quantifies the balance across arms with regard to a set of prespecified covariates (i.e. degree of prior PBIS implementation and school size). From a subset of possible assignments that achieve adequate balance, one is randomly chosen as the final allocation of interventions for the study.

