### Measures

Educators (principals/administrators, teachers, paraeducators) will complete secure web-based surveys via REDCap at three time points (Table 1). Time points will be baseline (April/May; T1) before the academic year in which schools will receive HELM, winter (Jan/Feb; T2, 8–9 months after baseline), and spring of the subsequent year (April/May; T3, 12 months after baseline). Educators will self-report their demographic characteristics, organizational mechanisms of change (implementation leadership and climate), implementation time and costs, and deidentified classroom-level outcomes. Educators will be compensated $40 for the completion of study instruments at each data collection timepoint.

**Table 1 Tab1:** Study Measures

Construct	Measure Description	Source	Time
School demographics	School size, student body racial/ethnic composition, % free/reduced lunch	A	T1

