	**Organizational Mechanisms**		
Implementation Leadership	*School Implementation Leadership Scale* (SILS; 15): Adapted from the original ILS [20], the SILS has 24 items loading onto 8 subscales: Proactive, Knowledgeable, Supportive, Perseverant, Communication, Vision, Available, and Distributed Leadership. Subscale internal consistencies range from 0.91 to 0.96, and scores correlate with other leadership measures	P DLT T	T1-T3
Implementation Climate	*School Implementation Climate Scale* (SICS; [48]): Adapted from the original ICS [21] includes 21 items loading onto 7 subscales: Focus on EBP, Educational Support for EBP, Recognition for EBP, Rewards for EBP, Use of Data to Support EBP, Existing Supports for EBP, and EBP Integration, with good internal consistency estimates (range: 0.81–0.90)	P DLT T	T1-T3
Burnout	*Maslach Burnout Inventory* (MBI; [49]): Burnout will be measured using the 22-item MBI. Respondents will use a 7-point Likert (“0-Never” to “6-Every Day”) to respond to items across three subscales: nine items measure emotional exhaustion (e.g., “I feel used up at the end of my workday”), five items measure depersonalization (e.g., “I feel I treat some students as if they were impersonal objects”), and eight items measure personal accomplishment (e.g., “I deal very effectively with the problems of my students”). Internal consistency was acceptable for burnout (α = .89), emotional exhaustion (α = .91), and personal accomplishment (α = .83). The lower estimate for depersonalization (α = .69) is consistent with extant research using the MBI-ES [50]	P DLT T	T1, T3
Implementation Citizenship Behavior	*Implementation Citizenship Behavior Scale (*ICBS; [51]): The School Implementation Citizenship Behavior Scale is a 12-item scale with four subscales. This study will evaluate 6 items loading onto 2 subscales: Helping Others and Keeping Informed. Research demonstrates acceptable reliability (αs = .88-.92) for all subscales	P DLT T	T1-T3
Coordination	*Team Process Scale (TPS): Coordination* [52]: Team-related processes will be measured using the 5-item Coordination response scale of the TPS. Respondents will use a 5-point Likert (“0 = not at all to 5 = to a very great extent”) to report the extent to which they perceive their team engages in effective team processes. Research supports the content and construct validity of several versions of this scale, including the 5-item Coordination response scale.	P DLT	T1-T3

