	**HELM Manipulation Check**		
HELM Fidelity	Coding of video recordings of HELM delivery	O	T1 -T3

Note: *A* Administrative data, *P* Principal, *DLT* distributed leadership team, *T* Teacher, *O* Trained observer; T1 = Baseline (Apr/May prior to HELM/PBIS delivery year), T2 = Jan/Feb, 9 months after baseline, T3 = Apr/May, 12 months after baseline

*Fidelity*. The study’s primary outcome is school-level PBIS fidelity, assessed using the Tiered Fidelity Inventory (TFI; [54]). Facilitated by an expert PBIS coach, school PBIS implementation teams will complete the TFI in both the HELM and control conditions. The TFI is designed to be used 1) for initial assessment to determine the degree to which a school is using PBIS-consistent practices; 2) as a guide for implementation of Tiers 1, 2, and 3 EBPs, and 3) to track PBIS implementation over time. TFI data will be collected at the same time points as educator data.

*HELM fidelity checklist*. This checklist will be used as a manipulation check to document HELM delivery (based on observations of recorded HELM trainings). HELM coaches will complete a standardized measure of dates specific steps were completed.

*Qualitative Focus Groups*. We will develop a systematic, comprehensive semi-structured focus group guide that draws from the EPIS framework to examine multilevel (i.e., intervention, individual, inner, and outer settings) determinants that explain what processes facilitated or hindered implementation [28]. We will generate questions that explore the most salient implementation determinants and mechanisms, and how implementation leadership and climate may interact with other relevant characteristics of the setting [57, 58].

*Administrative Data*. At the end of each school year, deidentified academic records by classroom will be requested for all participating schools to extract students’ attendance, discipline (office disciplinary referrals), and achievement (grades, standardized test scores). To assist in modeling, these data will be collected retrospectively for the year prior to HELM participation as well as each cohort’s HELM year.

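### Leadership and climate ratings from HELM-trained principals and leadership-team members are not separated from teacher ratings, so a rating shift in those raters alone could bias the HELM effect in either direction

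*Protocol article*

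**What the plan says.** **Who is treated.** Under Participants: "Principals and leadership teams will participate in HELM for schools assigned to that condition". Under Implementation strategies, the initial training for principals, DLT and district leaders will "cover developing strategic implementation leadership behavior and building a positive EBP implementation climate in their schools". These are the two constructs later scored as outcomes.

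**Survey used inside HELM.** Component 1 consists of 360º "surveys measuring implementation leadership and climate are administered to principals and educators at three time points". It continues: "These data will be synthesized into a detailed feedback report, which will be shared with the DLT". The report feeds the leadership development plan and the coaching, and final feedback is reviewed at graduation.

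**Who rates the outcomes.** Under Measures: "Educators (principals/administrators, teachers, paraeducators) will complete secure web-based surveys via REDCap at three time points". Table 1 gives principal, DLT and teacher as sources for both the SILS and the SICS at T1–T3. It states that "the SILS has 24 items loading onto 8 subscales", one of them distributed leadership. Sources differ by measure elsewhere in the table: team coordination comes from principals and DLT only, and the classroom behavior rating from teachers only.

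**Model.** The Abstract and the Data Analytic Approach describe time within educator (or classroom) within school. Neither mentions rater role.

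**Status of the outcome.** The Abstract will examine "whether HELM will show steeper gains than the control on implementation leadership (primary outcome". The Fidelity paragraph under Measures instead names school-level PBIS fidelity as primary. Leadership and climate also form Hypothesis 1b and are the RQ2a mediators.

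**The concern.** In HELM schools, some of the people scoring leadership and climate know their allocation and have been coached on both constructs. Principals score their own leadership on the SILS. DLT members score leadership in which they share. On the SICS both groups give unblinded perceptions of the school. Control principals and DLT members rate without that coaching.

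If coaching changes how these raters use the scale, the shift occurs in one arm, after baseline, in one class of rater. Randomisation does not remove it, because it arises after allocation. Baseline adjustment does not, because it is a change from baseline. A main effect for role does not, because the shift is a role-by-condition-by-time effect. A contrast over all raters cannot tell this from school-wide improvement, and the same score then enters the mediation model.

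**Working it through.** **Inputs from the article:** 42 schools, 21 per arm; 10 educators per school; school-level ICC 0.10 to 0.35; 50% of post-test variance explained by pretest; p < 0.05; minimum detectable effect sizes (MDES) 0.23 to 0.65.

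**Assumptions not in the article:** two-sided test; 80% power; the share of raters who are principal or DLT; the size of the rating shift. The last two are varied below.

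**1. The plan's own figure.** With J schools and n raters per school, SE = √(4 × [ICC + (1 − ICC)/n] × 0.5 / J), and MDES = (t₀.₉₇₅ + t₀.₈₀, J − 2 df) × SE.
- J = 42, n = 10, ICC 0.10: SE = √(4 × 0.19 × 0.5/42) = 0.095; MDES 0.273.
- J = 42, n = 10, ICC 0.35: SE = √(4 × 0.415 × 0.5/42) = 0.141; MDES 0.404.
- Using the mean of two post-tests adjusted for baseline, the factor 0.5 becomes (1 + √0.5)/2 − 0.5 = 0.354, and the MDES at ICC 0.10 is 0.230.
- A school-level outcome gives 0.627 with 42 schools and 0.643 with 40.

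The stated range is therefore plausible. The article does not state the power level or which outcome has which value, so this is not a strict reproduction. The range is not in dispute here.

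**2. Bias if the school does not change.** Bias in the all-rater contrast = trained share × shift. The false-positive rate comes from the noncentral t with 40 df and noncentrality bias/SE, for a single baseline-adjusted test before any false-discovery adjustment.

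| Trained raters of 10 | Shift (SD) | Bias (SD) | Rate, ICC 0.10 | Rate, ICC 0.35 |
|---|---|---|---|---|
| 1 | 0.5 | 0.05 | 8% | 6% |
| 2 | 0.5 | 0.10 | 18% | 11% |
| 4 | 0.2 | 0.08 | 13% | 9% |
| 4 | 0.3 | 0.12 | 23% | 13% |
| 4 | 0.5 | 0.20 | 54% | 28% |

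A normal approximation gives 24% and 14% in the fourth row. The 0.12 SD there is about half the smallest stated MDES (0.12/0.23 = 0.52); 0.20 SD nearly equals it. A downward shift of the same size gives the same bias with the opposite sign.

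**3. Price of a teacher-only contrast.** With 6 untrained raters left of 10, the SE ratio is √[(ICC + (1 − ICC)/6)/(ICC + (1 − ICC)/10)]:
- ICC 0.10: √(0.250/0.190) = 1.15; MDES rises from 0.273 to 0.313.
- ICC 0.35: √(0.458/0.415) = 1.05; MDES rises from 0.404 to 0.424.

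With only 4 left, the MDES is 0.357 and 0.449. All of these lie inside 0.23 to 0.65.

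**The case against.** The strongest reply is that this is an article whose analysis plan is not shown, and that scoring by informant is ordinary analysis-plan detail. No sentence says that the three sources are pooled. The Data Analytic Approach says that the method varies by outcome and describes the nested models only in general terms. That much stands: pooling is inferred from the definition of educators, the Table 1 sources and the nesting. But the article does fix the raters and the model structure, and followed as written they mix trained and untrained raters.

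Several stronger readings are tempting, and the article does not support them:
- **The feedback survey is the outcome survey.** The 360º survey is not named as the SILS or SICS. Constructs, respondents and number of time points match, and no other leadership or climate instrument is described, so identity is likely but remains an inference.
- **All these ratings are self-ratings.** Only principals' SILS scores clearly are. The Introduction defines climate as educators' perceptions, and educators include principals, so their SICS answers belong to the construct.
- **The HELM effect is inflated.** Coached leaders may judge themselves more strictly, or may report real gains. Direction is not established.
- **The bias is large.** With one trained rater in ten it is small. All educators in a school are to be invited, which could lower the trained share.
- **The trial's primary result is at risk.** That follows only if the Abstract's label prevails over the Fidelity paragraph.

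**Conclusion.** The point holds as a possible bias in either direction, of unknown size, which the stated design and model would not remove. It affects Hypothesis 1b and the leadership and climate mediators in RQ2a, and reaches a primary outcome only if leadership is primary as the Abstract says. Over the cases worked, the bias runs from 0.05 to 0.20 SD and the false-positive rate from 6% to 54%. These figures rest on an assumed trained share and an assumed shift common to all trained raters; they illustrate sensitivity and do not estimate what will happen. The case for acting rests less on any one of them than on the low cost of separating roles that Table 1 already distinguishes.

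**What to change.** For the SILS and SICS, prespecify:
1. Rater role (principal, DLT member, teacher or other staff outside the DLT) in the model, with a role-by-condition-by-time term.
2. The contrast from teachers not on the DLT, reported beside the all-rater contrast, with principal and DLT ratings shown separately.
3. The non-DLT teacher score as a stated sensitivity mediator in RQ2a.
4. The interpretation: an effect confined to principal and DLT ratings is read as changed leader perception, not as established school-wide improvement.

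It would also help to state whether the 360º survey is the T1–T3 SILS/SICS survey. A rule that the two contrasts must agree in size before an effect is claimed is not needed: such agreement would be hard to define, and the teacher contrast is less precise.

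The cost is analysis-plan wording, one further model per scale and the wider teacher-only interval. Teachers are also unmasked and, as educators, also answer the 360º survey, so this reduces the bias but does not remove it. The article reports no enrolment as of February 2025; the change is best made before outcome data are examined.

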### Research procedures

Focus Groups. To understand “hypothesis defying residuals” (i.e., schools where implementation leadership and climate are inconsistent with their documented implementation outcomes), schools whose observed change in fidelity from T1 to T3 is greater than 0.5 standard deviation away from their predicted change will be identified for invitation to a focus group, balanced between users and non-users and HELM and control conditions. School-level focus groups with up to 10 participants (approximately 45–60 min) will be conducted at a convenient time for identified educators via Zoom and audio recorded. Participants will be paid $100 for their time. Recordings will be transcribed prior to coding. The mixed methods design will be sequential in structure (quantitative data collected prior to qualitative data); the functions are sampling (using quantitative data to identify our qualitative sample) and expansion (using qualitative data to provide depth and breadth of understanding of the factors that contribute to implementation outcomes that deviate from our theory of change; i.e., QUAN + QUAL); and the process is connecting (the qualitative dataset will build on the quantitative dataset; 49).

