### Aim 2: Explore for whom, under what conditions, how equitably, and through which processes HELM works to improve outcomes, as well as its cost-effectiveness.

Research Question 2a. Are the effects of HELM on PBIS fidelity mediated by improvement in organizational mechanisms of change (i.e., implementation leadership and climate)?

Research Question 2b. Are the effects of HELM on student outcomes mediated via implementation outcomes (i.e., PBIS fidelity)?

Research Question 2c. Are the effects of HELM consistent and equitable across buildings or are they moderated by school contextual factors (e.g., school size, student body racial/ethnic diversity, free/reduced price lunch)?

Research Question 2d. What explains implementation success in schools where HELM’s explanatory model does not fit? What factors outside of the hypothesized mechanisms explain implementation success (i.e., high fidelity) in schools where HELM’s explanatory model does fit?

Research Question 2e. What are the costs and cost-effectiveness of HELM vs. PBIS implementation as usual?

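### RQ2d asks about schools where the HELM model fits, but the focus-group rule invites only schools that deviate from it, and the SD behind the 0.5 cut-off is not named

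*Protocol article*

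**What the plan says.** Research Question 2d, under Aim 2 of the protocol article, contains two questions. The first is: "What explains implementation success in schools where HELM’s explanatory model does not fit"? The second asks which influences other than the hypothesised mechanisms "explain implementation success (i.e., high fidelity) in schools where HELM’s explanatory model does fit".

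The selection of schools is set out under Research procedures, in the Focus Groups paragraph. The target is "schools where implementation leadership and climate are inconsistent with their documented implementation outcomes". The quantity used is the school's change in fidelity from T1 to T3, and a school whose change is "greater than 0.5 standard deviation away from their predicted change will be identified for invitation to a focus group". The invited schools are to be "balanced between users and non-users and HELM and control conditions". The same paragraph gives the purpose of the qualitative data as depth on the "factors that contribute to implementation outcomes that deviate from our theory of change".

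Two other places deal with the focus groups. The Qualitative Focus Groups paragraph under Measures describes the interview guide, and the Qualitative Analysis paragraph under Data analysis describes the coding. Neither adds a further group of schools.

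**The concern.** The research question and the sampling rule do not match. By the protocol's own definition, a school within 0.5 SD of its predicted change is one that the model describes adequately. The second half of RQ2d is about those schools, and the rule leaves them out.

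This also affects the first half. If a factor turns up in interviews at discordant schools, the team will want to know whether it is particular to them or common to all schools in the trial. That needs at least a few concordant high-fidelity schools for comparison, and the plan as written supplies none.

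A second gap is in the rule itself: it gives a multiple of a standard deviation without naming the standard deviation. Candidates are the SD of the model residuals, the SD of observed change, and the cross-sectional SD of the Tiered Fidelity Inventory (TFI) score. They give materially different invitation pools, and on the most natural reading the pool is more than half of the trial.

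**Working it through.** **Part 1: the two passages side by side**

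| School type | Asked about in RQ2d? | Eligible under the focus-group rule? |
|---|---|---|
| More than 0.5 SD from predicted change | Yes, first question | Yes |
| Within 0.5 SD of predicted change | Yes, second question | No |

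Balancing by use and by condition happens among the schools already identified. It can reduce the number interviewed but cannot bring in a school from the second row. This part rests on no numerical assumption.

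**Part 2: how many schools the rule would flag**

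The article states no expected number of flagged schools, so there is no figure to reproduce.

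Inputs from the article: a two-sided cut of 0.5 SD (Research procedures) and 42 schools, 21 per arm (Abstract, Participants, Power Analysis).

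Assumptions: normal residuals, and R² for the share of variance in fidelity change that the model explains. The article does not give this R². The Power Analysis assumes that pretests explain 50% of posttest variance; that is a different quantity and serves here only as a reference point.

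Share flagged = 2 × (1 − Φ(c)), where c is the cut in residual-SD units.

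*Residual SD.* c = 0.5. Share = 2 × (1 − Φ(0.5)) = 61.7%; 42 × 0.617 = 25.9 schools, or 21 × 0.617 = 13.0 per arm. The 95% binomial range is 20 to 32 schools. A simulation with the SD estimated from 42 residuals gave 61.8%.

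*SD of observed change.* c = 0.5/√(1 − R²).

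| R² | Share flagged | Schools of 42 | Not eligible |
|---|---|---|---|
| 0.25 | 56.4% | 23.7 | 18.3 |
| 0.45 | 50.0% | 21.0 | 21.0 |
| 0.50 | 48.0% | 20.1 | 21.9 |
| 0.75 | 31.7% | 13.3 | 28.7 |

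*Cross-sectional TFI SD.* c = 0.5/(√(2 − 2r) × √(1 − R²)), with pre-post correlation r = √0.50 = 0.707. The share is 51.4% at R² = 0, 45.1% at R² = 0.25 and 35.6% at R² = 0.50.

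*Shape of the residuals, residual-SD reading.* Laplace 49%, t with 5 degrees of freedom 55%, uniform 71%.

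The 61.7% arises from noise alone: it applies even if the theory of change is entirely right. On that reading 42 − 25.9 = 16.1 schools are never eligible; on the change-SD reading with R² = 0.50 it is 21.9.

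**The case against.** The strongest reply is that this is purposive sampling for exploratory qualitative work. The cut-off defines a pool for invitation, which is then balanced. It feeds no estimate or test, and the article does not say that every flagged school will be interviewed. A wide pool is useful: a 1 SD cut on the residual reading would leave about 13 schools (42 × 31.7% = 13.3) to spread over two balancing factors, before refusals. This stands. A reader might infer that 0.5 SD is too lax and should be replaced, but the documents do not support that. Nor do they support saying that two-thirds of schools would be flagged: on the residual and change-SD readings the normal-theory maximum is 62%, and the share falls below half on several others.

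A second reply is that RQ2d need not rest on focus groups alone, since burnout, citizenship behaviour, coordination and change fatigue are surveyed in both arms (Table 1). This stands in part. It would be too strong to say that the second question must go unanswered. However, the article links none of those measures to RQ2d, and its Qualitative Analysis paragraph assigns factors beyond the hypothesised mechanisms to the focus-group themes.

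A third reply is that a condensed article may leave comparison schools to the full protocol. This does not remove the point. The article gives an explicit rule and an explicit purpose, and both exclude the schools that its own research question names.

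A reader might also infer that the balance factor in "balanced between users and non-users and HELM and control conditions" is meaningless because all schools receive PBIS training. That does not follow: receiving training is not the same as using PBIS, the article expects implementation to vary between schools, and the term may refer to individual educators. It is undefined in the article, but it need not be replaced.

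**Conclusion.** The mismatch is real. Followed as written, the plan gives the second question of RQ2d no qualitative sample and the first question no concordant comparison. That conclusion comes from the text alone.

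The unnamed SD is a further defect. The Focus Groups paragraph speaks of residuals, which points to the residual SD. On that reading about 62% of schools (26 of 42) would be flagged under normal residuals even if the model were correct. On the SD of observed change with R² between 0.25 and 0.50, the figure is about 56% to 48% (24 to 20 schools). These shares rest on normality and an assumed R², and outside those assumptions they can be lower or higher. They show that the pool is large and depends on the reading. They do not show that the threshold is wrong.

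The consequence is confined to one research question in an exploratory aim. The Aim 1 comparisons of HELM with control are not affected.

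**What to change.** Three changes of wording:

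1. Reserve some of the focus-group slots in each arm for concordant high-fidelity schools, meaning those within 0.5 SD of predicted change and with a high T3 TFI score. The team should set in advance what counts as high. If the second question of RQ2d is not intended, remove it instead.
2. State that the SD is that of the residuals from the model that generates the predicted change.
3. Because the flagged pool is large, invite flagged schools in order of absolute residual within arm, so that the most discordant are approached first.

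The 0.5 SD threshold and the existing balance factors can stay. The cost is that slightly fewer discordant schools are interviewed for a given number of focus groups. The timing is favourable: the Discussion reports no enrolment as of February 2025, and schools cannot be selected until T3 fidelity is known.
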